### Aims of the trial

From a methodological point of view, effects should be studied by randomised controlled trials. Before spending large resources for an RCT, the feasibility of the programme should be tested, and there should be some probability that there will be an effect. Thus, the aims of the present study are:

1. On the individual level: to test the feasibility of the new physical activity programme according to the ACSM guidelines. The exercises were conceptualised and described in the previous subsection "Development of the exercise programme".

2. On the institutional level: to initiate and evaluate a cooperation between GPs and exercise specialists, for recruiting and supporting participants. The reasons for this procedure were given in the subsections "Approaching seniors at home and via general practitioners" and "Summary and consequences for programme development and trial methodology".

3. On the methodological level: to analyse the capability and functional effects of the programme including the special support scheme, and the adherence of the participants, thus gaining preliminary data for the preparation of a randomised controlled study. The decision criteria are laid down in subsection "Statistical analysis and decision-making on RCT preparation".

## Methods

### Study overview: settings, targets, design and registration

The trial targets on community-dwelling patients, aged 70 years or above, who visit their GP's surgery. Beneath the practices, the participants' homes are also settings of the intervention, where the exercises are conducted and data are collected (diaries). For a time table and flow chart see figure 1 in subsection "Interventions". Using the framework of Campbell et al. [1], the present study belongs to phase II and is to prepare a phase III study. The trial is designed as a single arm interventional trial and is registered at http://www.controlled-trials.com as ISRCTN58562962.

**Figure 1 F1:**
[figure not shown]
**Time table and flow chart of the trial**. The time table refers to the perspective of the participating subject. The procedure on the institutional level is described in subsection "Recruitment of subjects and time schedule".

### Recruitment of subjects and time schedule

Community-dwelling older adults will be recruited through GP surgeries. The recruitment period starts in April 2009 and ends in July 2009. The last participant is expected to finish the intervention in November 2009. In order to recruit a representative sample, all participants are recruited consecutively through (approximately 10) GP practices (motivated research practices associated to the Institute of General Practice and Family Medicine, University Witten/Herdecke) within predetermined time periods. All patients aged 70 years or above who are seen by the GP within his consultation hours (personal contact) within that time period are screened for eligibility. Exclusion for medical or other reasons (see exclusion criteria) is documented. If the physician considers a patient eligible for the study, the patient is informed about the study in detail by the physician and by an exercise therapist. The therapist spends the whole recruiting period in the practice to assist the GP and to document the recruitment process. After a participant has given written informed consent, appointments for the baseline assessment (telephone interview and motor tests in the practice, see secondary outcome measures) are made. The recruiting period for the respective physician ends with the recruitment of a predetermined number of patients. The recruitment period for the first participating practice ends with the recruitment of 12 patients. The number of participants to be recruited by the following practices depends on the number of patients that have already passed the baseline assessment in the previous practices. The target of this recruitment mode is that 90 subjects participate in the baseline assessment (on average 9 patients per practice if 10 practices participate in the study).

#### Inclusion criteria

To be eligible for this study, patients have to be aged greater than or equal to 70 years. All participants need medical clearance from their GP to participate in the study. They have to be able to walk (with or without a walking aid) and to visit the practice of the GP for repeated consultations. Furthermore, participants have to be able to cooperate appropriately and to follow the instructions of the home-based exercise programme (according to their GP's judgement). Finally, all participants have to provide written informed consent.

#### Exclusion criteria

Patients are excluded if the intervention doesn't fit into their schedule (e.g. because of a planned vacation). Patients are excluded for medical reasons if they suffer from untreated arterial hypertension or arterial hypertension despite antihypertensive medication (GP's judgement), from chronic heart failure (New York Heart Association (NYHA) grade III–IV), from an acute psychiatric disorder (e.g. depression), or from a severe consuming illness. Furthermore, patients are excluded, if they suffered a clinically relevant cardiovascular event (e.g. unstable angina pectoris, myocardial infarction, coronary angiography and/or angioplasty, cardiac surgery), a clinically relevant cerebrovascular event (e.g. stroke, recurrent TIA), any inpatient surgical procedure, or a deterioration of an insufficiently controlled diabetes mellitus (according to their GP's judgement) within the past 3 months, or if their HbA1c exceeds 10% (if available). Concurrent participation in another clinical trial is also an exclusion criterion.

#### Risk-benefit considerations

Unlike some physical activity trials that often exclude chronically diseased individuals this study only excludes individuals that are at high risk for adverse events. The GP, who knows the participant's medical history and his current health status, decides whether the patient is eligible for the programme. For the patients who are eligible for the study, the expected cardiovascular benefit of the programme exceeds the risk for adverse cardiovascular events. Cardiovascular risk is not the only risk associated with starting an exercise programme. An increase of physical activity and especially of walking outdoors may initially increase the risk of minor and major musculoskeletal injuries (including sprains, strains, joint pain, overuse injuries, falls and fractures) compared to a sedentary lifestyle. But in the long term, an increase in physical activity is considered to lead to a better mobility, to an improvement in gait performance and consecutively to a reduction of fall and injury risk. To reduce the risk of adverse events, the exercise programme is tailored to the abilities of the patient by an exercise therapist (in cooperation with the GP) who holds a university degree in sports science (bachelor or higher).

### Interventions

The intervention lasts 12 weeks and consists of physical activity counselling, the previously described home-based exercise programme, and exercise consultations provided by an exercise therapist in the GP's practice and via telephone. The exercise programme starts immediately after the baseline assessment in the GP's practice (week 1) and ends with the final assessment in the practice (week 13, see figure 1).

#### Physical Activity Counselling and Exercise Consultation

The exercise therapist provides initial counselling on general aspects of physical activity (week 1), an introduction (theoretically and practically) into the exercise programme (week 1), a given number of additional personal consultations within the practice of the participant's GP (week 2, 4 and 6), and a given number of consultations on the telephone (week 3, 5, 7, 9 and 11). First of all, the participant receives standardised counselling by the exercise therapist pertaining to the benefits of physical activity (week 1). The conversation is aiming to improve knowledge and understanding of the preventive and therapeutic effects of physical activity on particular chronic conditions. The counselling also contains a systematic assessment of the actual physical activity status, a discussion of potential barriers, problem solving to overcome barriers (e.g. by creating an activity timetable), and the creation of individual physical activity goals. Secondly, based on the assessment of the actual physical activity habits and the functional abilities of the participant and based on the knowledge of the participant's chronic diseases (communicated by the GP), the exercise therapist adapts the exercise programme to the participant's abilities and needs, integrating preventive and therapeutic aspects. Every participant is taught (theoretically and practically) to correctly perform the selected exercises (week 1). A pictorial guidebook is provided to each participant to assist them in correct exercise performance. Within the following personal consultations (week 2, 4, 6) with the exercise therapist, the participant gets the opportunity to discuss problems concerning the exercise programme. Exercises are controlled for correctness of performance. New exercises are taught. Choice and intensity of exercises is adapted to the participant's performance level. The consultations aim to provide encouragement and to improve knowledge and self-efficacy of the participants so that they are able to perform their activity programme independently. Support is reduced in a stepwise manner and personal consultations are replaced by telephone consultations (week 3, 5, 7, 9 and 11). If a patient misses a personal consultation in the practice, the appointment is replaced by a telephone consultation. Every consultation follows a standardised protocol and is documented by the exercise therapist.

#### Home-based exercise programme

The exercise programme (described in section "Development of the exercise programme") consists of two main components that should be performed in alternating order:

1. a combination of home-exercises to improve strength, flexibility and balance on 3 days of the week,

2. walking to improve aerobic capacity on 4 days of the week.

Every participant is instructed and supervised by his personal exercise therapist. The exercise programme usually starts with a selection of a few simple home-exercises and with short walks. Additional exercises are taught by and by (depending on the participant's progress) with the advancement of the intervention. The duration of the walks is also increased in a stepwise manner. Days of rest are accepted according to the patient's needs. In case a participant is able to perform all home-exercises, he performs ten strengthening exercises (moderate intensity 5–6/10), followed by four flexibility exercises and two balance exercises. The exercises are numbered and should always be performed in the same chronological order. To perform all home-exercises in a row it takes about 30 to 45 minutes. In case of questions or problems concerning the exercise programme, patients have the opportunity to contact their GP or their exercise therapist.

#### Materials

##### Pictorial guidebook

The pictorial guidebook includes a statement of the activity goals and general information on the exercise programme (frequency, duration, intensity), instructions for use of the pedometer and the elastic resistance bands, safety instructions, instructions for clothing and warm-up, a detailed description of all home-exercises, and contact information of the exercise therapist (including the mobile phone number). The pictorial guidebook has been developed using older adults as models.

##### Workbook

Every participant receives the German Olympic Sports Federation workbook "Bewegungsangebote 70 plus" [Physical activity choices 70 plus] [50] that includes general information on the health benefits of physical activity and detailed information about physical activity programmes for seniors in Germany.

##### Elastic resistance bands

Elastic resistance bands are provided to the participants in order to perform some of the home-exercises. The elastic resistance bands (Thera-Band^® ^GmbH, Dornburg-Frickhofen, Germany) are available in eight different colour-coded levels of resistance. Two different levels of resistance, that are rather low within the available spectrum, have been chosen for this study: the yellow band ("thin") provides lower resistance; the red band ("medium") provides higher resistance. If necessary, additional resistance can be created by folding the band. Every participant gets a yellow and a red band, each of them measuring two metres.

##### Pedometer

As a motivational support and to receive immediate feedback on their accumulated step count, every participant gets a pedometer (NL-800, New-Lifestyles Inc., Lee's Summit, USA). The pedometer measures vertical acceleration to count steps. It has an internal memory chip and is capable of storing up to 7 days of data, in 1-d epochs. The internal clock resets the step count at midnight. Step total is displayed on a screen. The pedometer should be worn close to the hip, attached to a belt, waistband or a horizontal pocket. Participants are instructed in the use of the pedometer and asked to begin recording daily pedometer counts (every evening).

##### Activity Log

Patients are instructed to record their daily activity. The activity log serves as a motivational support and as a help for the therapist to supervise (and adapt) the exercise programme. The following items are recorded by the patients every day: duration of walking for exercise, performance of home-exercises, total step count, comments (e.g. reasons for inactivity). The activity log also serves as an outcome measure.

##### Consultation protocol

The exercise therapist completes a structured protocol for every consultation (personal/telephone). The protocol serves as a documentation of the participant's progression and as a help for the therapist to pick up on the last consultation and to further develop the participant's exercise programme. The following items of the protocol are based on a structured dialogue between the therapist and the participant: general well-being of the participant, activity log use (problems, documentation of exercises and steps, inactivity), pedometer use (problems, usage, frequency and duration of use), walking for exercise (problems, frequency, intensity, duration), home-exercises (problems, chosen exercises, frequency, intensity, duration), medical consultations (reason, specialisation of the consultant) or hospital admissions (reason, hospital department). During the personal consultations in the GP's practice, the structured dialogue is followed by an assessment of the correctness of exercise performance (correction, adaptation of resistance, progression from "basic" to "intensive" exercises) and by rehearsing new exercises. At the end of the consultation, the patient gets an adapted exercise programme (duration and intensity of walks, selection of home exercises), that is documented in the consultation protocol and in the participant's activity log. The consultation protocol may be analysed and used as an outcome measure in case of drop-outs.

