##### Documentation of any undesirable event during the intervention

Any symptom or disease of any participant, which occurs during the intervention, is called an undesirable event. This definition is valid without reference to the fact, whether the intervention might be a cause or not. In case of an undesirable event, the participant promptly has to suspend exercise and to visit the surgery. The event has to be documented by a standardised report protocol, including the following judgements by the physician: medical/non-medical; caused/not caused by exercise; subject may/may not continue exercises.

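### Undesirable events rely on participants coming to the surgery, while the therapist's record of medical consultations and admissions has a stated outcome use only for drop-outs

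*Protocol article*

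**What the plan says.** Protocol article, *Documentation of any undesirable event during the intervention* (under *Primary outcome measures*), defines the outcome broadly: "Any symptom or disease of any participant, which occurs during the intervention, is called an undesirable event". Cause plays no part: "This definition is valid without reference to the fact, whether the intervention might be a cause or not". The route into the data is: "In case of an undesirable event, the participant promptly has to suspend exercise and to visit the surgery". A report then follows: "The event has to be documented by a standardised report protocol, including the following judgements by the physician". Those judgements cover whether the event is medical, whether exercise caused it, and whether the participant may go on.

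Protocol article, *Consultation protocol*, describes a second record: "The exercise therapist completes a structured protocol for every consultation (personal/telephone". Its items include general well-being, problems with walking and with the home exercises, and "medical consultations (reason, specialisation of the consultant) or hospital admissions (reason, hospital department". On outcome use it says: "The consultation protocol may be analysed and used as an outcome measure in case of drop-outs".

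The section just before it, *Activity Log*, states without any condition that the log is also an outcome measure.

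**The concern.** The two records overlap in content but not in stated use. The event report depends on the participant coming forward. The consultation protocol is active: the therapist asks everyone, at fixed times, and asks which specialist was seen, so the plan itself expects care outside the GP's surgery. A hospital admission or specialist visit prompted by a symptom or illness meets the event definition. Yet no stated step carries it from the therapist's form into the event report if the participant continues in the programme.

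At stake is the completeness of a primary safety description in a study meant to supply preliminary data for a randomised trial. The definition is wide and the participants are 70 or older. The *Background* reports that some 80% of Germans aged 70 to 85 state two or more chronic diseases. Many qualifying complaints can be expected, and not every one need bring the participant promptly to the GP.

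**Working it through.** The article gives no event rate, capture rate or event-count target, so there is no figure of the plan to reproduce on this point. The check is a comparison of the sections, followed by an illustration under stated assumptions.

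**1. The two records side by side**

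| | Undesirable-event report | Consultation protocol |
|---|---|---|
| Who is covered | any participant | every participant, at each consultation held |
| How it starts | participant visits the surgery | therapist asks |
| Completed by | standard report with physician's judgements | exercise therapist |
| Stated outcome use | primary outcome | permitted in case of drop-outs |

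*Measures of adherence* also uses consultations, but it counts those attended, not the medical information recorded in them.

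**2. How much information is involved**

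Inputs: personal consultations in weeks 2, 4 and 6, and telephone consultations in weeks 3, 5, 7, 9 and 11 (*Physical Activity Counselling and Exercise Consultation*); 90 participants and an assumed drop-out rate of 45% (*Sample size*).

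- Contacts per participant after week 1: 3 + 5 = 8.
- Participants who complete: 90 × (1 − 0.45) = 49.5.
- Forms from them: 49.5 × 8 = 396.

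This is approximate. The 45% is the assumption for the adjusted drop-out rate, and full attendance is assumed. It counts forms, not missed events.

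**3. What incomplete reporting would do (assumed values only)**

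Let the true proportion of participants with an event be 30% in both groups, and let *c* be the share captured through the surgery route.

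- Case A, the record adds events for nobody: observed = 0.30 × *c*, the same in both groups.
- Case B, the record completes the count for drop-outs alone: observed overall = 0.30 × (0.45 + 0.55 × *c*). Drop-outs show 30% and completers 0.30 × *c*.

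| *c* | A: overall | B: overall | B: drop-outs vs completers |
|---|---|---|---|
| 1.0 | 30% | 30% | 30% vs 30% |
| 0.9 | 27% | 28.4% | 30% vs 27% |
| 0.7 | 21% | 25.1% | 30% vs 21% |
| 0.5 | 15% | 21.8% | 30% vs 15% |

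The relative shortfall is 1 − *c* in case A and 0.55 × (1 − *c*) in case B. At *c* = 0.7 that is 30% and 16.5%. With full capture there is none. Case A lowers the count evenly; case B lowers it less but creates a gap between groups that truly have the same rate.

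**4. Link to the decision criteria**

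Criterion 2 is met when more than 30% of participants have to stop exercising for medical reasons judged probably caused by the intervention: 0.30 × 90 = 27, so 28 or more. These are discontinuations, and *Measures of drop-out* requires a reason for each. An unreported event in someone who carries on does not enter that number. The indirect path is that an event never reported never receives the physician's judgement on cause and on continuing. Criteria 1 and 3 do not use events.

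**The case against.** The strongest reply has four parts.

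- **The wording is permissive.** The sentence allows a use in case of drop-outs. It forbids no other use and does not name the form as an event source for anyone. It may only mean that the last consultation records help to explain why someone left.
- **The event route is the same for everyone.** One definition and one report form apply to completers and drop-outs alike.
- **The therapist and the GP work together.** Personal consultations take place in the practice, so an event first mentioned to the therapist may well reach the physician.
- **This is an article.** Reconciling two records is a detail that a full protocol may hold.

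Much of this stands, and it limits the point. A reader might infer that the event count is too low. The documents do not show that, because they give no capture rate. A reader might also infer that ascertainment is already uneven. That would need events to be added from the therapist's record for drop-outs alone, which no section says, and no comparison of event rates between drop-outs and completers is planned. Any percentage shortfall is pure assumption, and a direct effect on criterion 2 is ruled out by how that criterion is worded.

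The last part of the reply does not dispose of the point. The article is not silent on outcome use of this record. It states one, tied to drop-out, directly after stating an unconditional one for the activity log. That fits badly with a primary outcome covering every participant. Informal contact between therapist and GP is likely, but it is not a stated step.

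**Conclusion.** The point holds as a risk. The primary event outcome rests on participants presenting at the surgery, while a record that actively asks everyone about medical consultations and admissions has a stated outcome use only for drop-outs. Events of continuing participants can therefore be in the trial's files without being counted or judged by the physician.

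The direction of the risk is clear (too few events), but its size cannot be computed from the documents. The tabulated values rest on an assumed 30% event proportion, equal in both groups, and on assumed capture rates. Differential ascertainment is conditional on the record being used to add events for drop-outs alone. The effect falls on the safety description and on planning of the randomised trial, and at most indirectly on criterion 2.

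**What to change.** In *Consultation protocol*, replace the use tied to drop-outs with a statement that the consultation protocols of all participants serve as a source for undesirable events. Then:

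1. List the recorded medical consultations, hospital admissions and health problems, and check them against the undesirable-event reports.
2. For each unmatched item that meets the article's event definition, have the physician complete the standard report, including its judgements.
3. Count events from the reconciled list, in the same way for completers and drop-outs.

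It would help to report how many events came from each source, since that shows how complete the surgery route was.

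No new data are needed. The cost is some reconciliation work and additional report forms. The event rate may look less favourable than one based on surgery visits alone.
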